#### Feasibility and satisfaction measures

The proportion of our minimum recruitment target of 6 participants that we achieve will be reported. Successful completion of 6 participants will indicate that the recruitment protocol is feasible. The proportion of participants retained, defined as completing both the baseline and intervention assessments will be reported; with an 80% retention rate indicating that the research protocol is feasible, based on previous studies [71]. We will also report the proportion of appointments attended across all participants. The key themes identified in the Experience of Services Questionnaire [39] and the questionnaire assessing the impact of COVID-19 or other events on the child’s loneliness will also be reported. Acceptability will be indicated by 80% positive responses on the Experience of Services Questionnaire [39].

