### Aims and objectives

The primary objective will be to evaluate the efficacy of CBT for loneliness in children and young people ages 11–18. The primary outcome will be differences in scores on the Three-Item Loneliness Scale [34] between baseline and intervention and baseline and post-intervention. It is hypothesised that there will be a significant decrease in self-reported loneliness across both time-points. The secondary outcomes will be self-reported loneliness scores on the UCLA Loneliness Scale (UCLA-LS-3) [35] and self and parent-reported scores on the Strengths and Difficulties Questionnaires (SDQ) [36] and Revised Child Anxiety and Depression Scale (RCADS) [37]. It is hypothesised that there will be a reliable and clinically meaningful change [38] in total loneliness scores on the UCLA-LS-3, in the impact scores on the SDQ and in total anxiety and depression scores on the RCADS.

The secondary objective is to evaluate the feasibly and acceptability of the intervention process. This will be defined in terms of a) meeting the recruitment target, b) participant retention and c) participant feedback of the intervention using the Experience of Service Questionnaire [39].

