### Participants

We will aim to recruit 6–8 participants to the study. All participants will be recruited from within the United Kingdom. Participants must meet the following inclusion/exclusion criteria:

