#### Feasibility and experience measures

During the post-intervention assessment, the participants will be asked to complete the child and parent-report versions of the Experience of Services Questionnaire (ESQ) [39] regarding their experience of the intervention. Feasibility will be assessed based upon recruitment (meeting targets), retention, completion of measures and proportion of sessions attended by the participants. All participating families will also be asked how COVID-19 or other events have impacted the child’s loneliness during the intervention period. Finally, any adverse events that occur during the trial period will be recorded, reported and discussed within supervision.

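### The recruitment feasibility rule counts completers instead of recruits, so at the minimum sample size it can fail a study that met its recruitment target and passed its retention rule

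*Protocol article*

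**What the plan says.** The Participants section of the protocol article gives the planned size: "We will aim to recruit 6–8 participants to the study". Aims and objectives defines feasibility and acceptability by components, the first two being "a) meeting the recruitment target, b) participant retention". The outcome section headed Feasibility and experience measures makes the same split, naming recruitment in terms of targets and listing retention separately.

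The decision rules are in the data analysis section, under Feasibility and satisfaction measures. Three consecutive statements matter:

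- Reporting of recruitment: "The proportion of our minimum recruitment target of 6 participants that we achieve will be reported".
- Verdict on recruitment: "Successful completion of 6 participants will indicate that the recruitment protocol is feasible".
- Retention: this is tied to finishing the assessments at both ends of the study, and the threshold attached to it is given in these words: "with an 80% retention rate indicating that the research protocol is feasible".

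**The concern.** The first statement measures recruitment by how many participants are recruited against a target of 6. The second passes or fails recruitment on how many complete. The third uses completion again, this time as the definition of retention, with a more lenient threshold at the minimum sample size.

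Once 6 participants are enrolled, the recruitment verdict no longer depends on recruitment. It depends only on how many stay. A study that recruited everyone it set out to recruit could then have to report that its recruitment procedure was not shown to be feasible, because of a single dropout that its own retention rule tolerates. Feasibility is a stated objective, so a mislabelled verdict would attribute a retention event to the recruitment process.

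**Working it through.** **Inputs**

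- Planned N: 6, 7 or 8 (Participants).
- Recruitment target: at least 6 recruited (Feasibility and satisfaction measures, first statement).
- Recruitment decision rule: at least 6 completers (same section, second statement).
- Retention rule: completers/N of at least 0.80 (same section, third statement).
- Completion probability p: not given in the documents. The 80% is a pass threshold, not a forecast. It is used below as an assumed value, with a range of 0.70 to 0.95.

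The plan derives no figure from these rules, so there is nothing of its own to reproduce first.

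**Step 1. Completers each rule needs**

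The retention rule needs the smallest k with k/N ≥ 0.80. The recruitment rule needs k = 6 at every N.

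| N | Recruitment target met? | Retention rule needs | Recruitment rule needs | Retention implied by recruitment rule |
|---|---|---|---|---|
| 6 | yes | 5 (5/6 = 83.3%) | 6 | 6/6 = 100% |
| 7 | yes | 6 (6/7 = 85.7%) | 6 | 6/7 = 85.7% |
| 8 | yes | 7 (7/8 = 87.5%) | 6 | 6/8 = 75% |

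**Step 2. The case that goes wrong**

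N = 6 with 5 completers: recruitment is 6/6 = 100% of target and retention is 83.3%, which passes. The recruitment rule needs 6 completers and has 5, so it is not met.

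At N = 7 or 8 the recruitment rule also fails with 5 or fewer completers although the target is met. Retention fails there as well (5/7 = 71.4%, 5/8 = 62.5%), so the attrition is flagged under its proper name too.

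**Step 3. How often the recruitment rule is met when the target is already met**

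P(at least 6 complete) = Σ from k = 6 to N of C(N,k) p^k (1−p)^(N−k). With p = 0.80:

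- N = 6: 0.8^6 = 0.262
- N = 7: 7 × 0.8^6 × 0.2 + 0.8^7 = 0.367 + 0.210 = 0.577
- N = 8: 28 × 0.8^6 × 0.2^2 + 8 × 0.8^7 × 0.2 + 0.8^8 = 0.294 + 0.336 + 0.168 = 0.797 (unrounded terms)

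At N = 6 the retention rule is met with probability 6 × 0.8^5 × 0.2 + 0.8^6 = 0.393 + 0.262 = 0.655. The difference, 0.393, is the probability of exactly 5 completers, that is, of the anomalous result in Step 2.

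**Step 4. Sensitivity to the assumed p**

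| p | Recruitment rule met, N = 6 | N = 7 | N = 8 | Retention rule met, N = 6 |
|---|---|---|---|---|
| 0.70 | 0.118 | 0.329 | 0.552 | 0.420 |
| 0.80 | 0.262 | 0.577 | 0.797 | 0.655 |
| 0.85 | 0.377 | 0.717 | 0.895 | 0.776 |
| 0.90 | 0.531 | 0.850 | 0.962 | 0.886 |
| 0.95 | 0.735 | 0.956 | 0.994 | 0.967 |

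If recruitment were judged on recruits, its verdict would be a pass in every cell of the three recruitment columns.

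**The case against.** The best defence has four parts.

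*Completion may be loose wording for recruitment.* That is possible, but the text does not say so, and the very next sentence uses completing assessments to define retention. A reader applying the rule as written would count completers.

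*The rules do not contradict each other.* This stands. One judges the recruitment protocol and the other the research protocol, so both verdicts can formally be reported together. Six completers also require at least 6 recruits, so the rule mixes recruitment and retention; it becomes a pure completion test only once 6 are enrolled. The clash is with the preceding sentence and with the two sections that keep recruitment and retention apart.

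*The 26% is the worst case.* This stands too. The plan of 6–8 leaves room for attrition, the figure rises to 58% and 80% at N = 7 and 8, and it depends on an assumed completion rate.

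*The reported figures would expose the anomaly.* Largely true: the proportions recruited and retained will both be reported. That limits the harm, but a pass/fail rule should not need correcting by the figures beside it.

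Three stronger readings are tempting but unsupported:

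- A reader might take 8 recruited with 6 completing (recruitment passes, retention fails at 75%) as a second error. Counting recruits gives the same two verdicts, so it shows no fault.
- A reader might extend the criticism to the 80% acceptability rule, because the Experience of Service Questionnaire is given at the post-intervention assessment. The article does not say that families who stop early are denied that assessment or are the least satisfied, and it does not state that the 80% is counted over families. Scoring non-response as not positive would also count attrition twice.
- A reader might infer that the verdict decides whether an open trial or RCT follows. The Limitations section ties that step to preliminary evidence of effectiveness, not to feasibility.

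**Conclusion.** The point holds in limited form. The recruitment decision rule is written on the wrong quantity: it counts completers where the preceding sentence, Aims and objectives, and Feasibility and experience measures all treat recruitment as reaching a target, separate from retention. The two thresholds are inconsistent rather than contradictory. The clear failure is at N = 6 with 5 completers, and it follows from the text without any assumption. The 26%, 58% and 80% rest on an assumed 80% completion probability, independent across participants. At N = 6 the figure runs from 12% to 74% over assumed probabilities of 0.70 to 0.95.

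The consequence is confined to the feasibility objective. The rule should be corrected because, followed as written, it can give a wrong verdict on recruitment, and the correction is simple.

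**What to change.** In Feasibility and satisfaction measures, replace the recruitment rule by one stating that recruitment is judged feasible if at least 6 eligible participants are recruited and randomised. Leave completion entirely to the 80% retention criterion, and state that its denominator is all randomised participants.

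With 6 recruited and 5 completing, recruitment is then met (6/6) and retention is met (83.3%), each on its own quantity. If the investigators do want 6 complete cases, for example to support replication across participants, that can be kept as a separate criterion under its own name.

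The cost is a sentence or two of wording. No data collection, sample size or primary analysis changes.

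### The recruitment feasibility criterion is worded on completers, so dropout after a fully met recruitment target would be recorded as a recruitment failure

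*Protocol article*

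**What the plan says.** The planned size is given under Participants: "We will aim to recruit 6–8 participants to the study".

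Aims and objectives defines feasibility and acceptability through components that include "a) meeting the recruitment target, b) participant retention". Feasibility and experience measures repeats the separation: "Feasibility will be assessed based upon recruitment (meeting targets), retention, completion of measures".

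Feasibility and satisfaction measures then sets the rules, in this order:

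- What is reported for recruitment: "The proportion of our minimum recruitment target of 6 participants that we achieve will be reported".
- What decides recruitment: "Successful completion of 6 participants will indicate that the recruitment protocol is feasible".
- What is reported for retention: "The proportion of participants retained, defined as completing both the baseline and intervention assessments will be reported".
- What decides retention: "with an 80% retention rate indicating that the research protocol is feasible".

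**The concern.** The statistic reported for recruitment is measured against a target number of recruits. The verdict on recruitment rests, in the next sentence, on a number of completers. These are different quantities as soon as anyone drops out, and the article has a separate rule for dropout.

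Whether families can be found and whether they stay are different questions with different remedies. If the recruitment verdict falls because someone left, the trial would point to a recruitment problem that it did not have. With six to eight participants, one dropout can decide the verdict. The unit being counted should therefore be fixed before dropout is known.

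**Working it through.** The article derives no sample size or power from these criteria, so there is no stated figure to reproduce. The check is an enumeration.

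**Inputs**

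- Number enrolled, n: 6, 7 or 8 (Participants).
- Recruitment target: at least 6 (Feasibility and satisfaction measures).
- Recruitment rule as worded: completers c ≥ 6 (same section).
- Retention rule: c/n ≥ 0.80 (same section; the stated 80% is read as at least 80%).

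**Step 1. Completers needed for 80% retention**

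- n = 6: 0.80 × 6 = 4.8, so 5 are needed (5/6 = 83.3%).
- n = 7: 0.80 × 7 = 5.6, so 6 are needed (6/7 = 85.7%).
- n = 8: 0.80 × 8 = 6.4, so 7 are needed (7/8 = 87.5%).

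**Step 2. Recruitment verdict as worded against the recruitment target**

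Every n from 6 to 8 meets the target of at least 6 recruits. The rule as worded gives the same verdict when c ≥ 6 and the opposite verdict when c ≤ 5. That takes one dropout at n = 6, two at n = 7 and three at n = 8. The boundary cases are:

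| Enrolled | Complete | Retention | 80% rule | Target of 6 recruits | Recruitment rule as worded |
|---|---|---|---|---|---|
| 6 | 5 | 83.3% | pass | met | fail |
| 7 | 5 | 71.4% | fail | met | fail |
| 8 | 5 | 62.5% | fail | met | fail |

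In all three rows the recruitment failure comes only from dropout. The first row is the clearest: the target is met in full and retention is acceptable by the article's own standard, yet recruitment is judged not feasible.

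**Step 3. How often the 5-of-6 outcome could arise**

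This needs assumptions that the article does not supply: exactly 6 enrolled, independent dropout and a true retention probability p. Then P(5 of 6) = 6 × p⁵ × (1 − p).

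- p = 0.80: 6 × 0.3277 × 0.20 = 0.393
- p = 0.85: 0.399
- p = 0.90: 0.354
- p = 0.95: 0.232

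If only six are enrolled, the outcome is therefore not remote, with a chance of about 0.23 to 0.40 over this assumed range.

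**Step 4. The same outcomes if recruits are counted**

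With the recruitment rule set at n ≥ 6, all three rows in the table pass recruitment. Retention then separates them: 5 of 6 passes, while 5 of 7 and 5 of 8 fail. Each verdict then measures what it is named for.

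**The case against.** Four points can be made for the plan.

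**The sentence may be loosely worded.** It directly follows the recruitment target, and its subject is the recruitment protocol. It does not define completion, whereas the retention sentence does define its own term. It could mean finishing the recruitment of six. On that reading no wrong verdict arises. This stands as a possibility and limits how firmly one can say that completers were intended. The plain sense of completion of participants is still that they finish, and the two readings give different verdicts, so the sentence needs rewording in either case.

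**There is no contradiction with the 80% rule.** A reader might infer that the two criteria conflict because they can return different verdicts. The article does not support that. One criterion concerns the recruitment protocol and the other the research protocol, and nothing requires them to agree. Six completers out of eight (75%) passes recruitment and fails retention as worded, and does the same when recruits are counted. That is a coherent result and no evidence of a fault.

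**A large failure probability is easy to quote but not warranted.** With exactly six enrolled and true retention of 80%, the chance of fewer than six completers is 1 − 0.8⁶ = 0.74. A reader might take this as the risk of a false verdict. The article aims for six to eight, and its 80% is a pass mark, not a forecast. Under the same assumptions the retention rule also fails about 34.5% of the time (1 − 0.655).

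**Little depends on the verdict.** The proportions recruited, retained and attending will all be reported, so a reader can see what happened. Feasibility is not the primary objective, and the Limitations section makes the next study depend on preliminary evidence of effectiveness. This stands and keeps the point modest. It does not make the stated rule right.

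**Conclusion.** The point holds in a narrow form. The recruitment criterion, as worded, counts completers. That is inconsistent with the recruitment target in the sentence before it and with the two other sections that define recruitment as meeting a target, apart from retention. Within the planned enrolment, the wording changes the recruitment verdict whenever fewer than six complete. In one of those outcomes, 5 of 6, it declares recruitment a failure although the target was met and retention passed.

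This rests on reading completion as participants finishing and 80% as at least 80%. It does not rest on any assumed dropout rate; the probabilities in the working only illustrate. The primary analysis is unaffected. This is not a gap that a fuller protocol or an analysis plan would be expected to fill, because the article itself states the rule.

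**What to change.** Reword the deciding sentence so that recruitment is judged feasible if at least six eligible participants are consented and randomised. Leave completion to the 80% retention rule alone, which means at least 5 of 6, 6 of 7 or 7 of 8.

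If six completers is what the authors want, keep it as a separately labelled completion criterion and do not use it to judge recruitment.

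The cost is one sentence. No trial procedure, data collection or analysis changes. An exact confidence interval for the retention proportion could be added but is optional.

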#### Data management, confidentiality and access

All data in the trial is anonymised. Participants will complete their questionnaires via Qualtrics [41], which is a password protected online platform. Consent forms will be stored on a separate encrypted database to participant data and linked by a unique participant ID number. Anonymised data will made available within the OSF data repository.

#### Patient public involvement (PPI)

A young person advisor and several parent/carer advisors provided advice on the study advertisements, information sheets, assessment protocol and intervention materials. A member of the University College London Loneliness and Social Isolation in Mental Health Research Network provided feedback on the intervention protocol. As the intervention protocol is being developed iteratively using PDSA cycles [31] it will also be adapted based upon within-session feedback from the participants.

## Discussion

To the best of our knowledge this will be the first study to test a CBT-based intervention for loneliness in young people ages 11–18. The intervention is modular and based upon Käll et al., [23] cognitive behavioural analysis of chronic loneliness. The intervention incorporates translated elements of Käll et al., [55] online intervention, and is informed by MATCH-ADTC [50], Groups4Health [51], PEERS social skills training [52] and CBT for Social Anxiety Disorder for adolescence [53]. The intervention will be evaluated through a SCED [28–30] of 6–8 participants. The primary objective of this study will be to test the efficacy of the intervention in terms of whether there are differences in scores on the Three-Item Loneliness Scale [34] between the different phases. The secondary objectives will be to examine whether there is reliable and clinically meaningful change [38] in self-reported loneliness scores on the UCLA-LS-3 [35], self and parent-reported impact scores on the SDQ [36] and self and parent-reported total scores on the RCADS [37]. The third objective will be to evaluate the feasibly and acceptability of the intervention. This will be defined in terms of a) meeting the recruitment target, b) participant retention and c) participant feedback of the intervention using the Experience of Service Questionnaire [39]. The results of the trial will be published in a peer reviewed journal and presented at relevant conferences.

### Limitations

The population of young people who are at an elevated risk of loneliness is highly heterogenous, [10, 11, 15, 16], and there is significant variability in the psychological problems across the 11–18 age range used in this study. The relatively small sample size means that it is not possible within this design to test the efficacy of the intervention broadly across these different subgroups. However, we suggest that the modular approach allows for the intervention to be applied flexibly, and so is feasible for use with the heterogenous population of young people presenting with chronic loneliness. If it is found that there is preliminary evidence that the modular intervention is effective, future research should examine the specific mechanisms maintaining loneliness for different subgroups of young people. This could allow for the development of bespoke adaptations of the intervention which may result in increased treatment engagement and efficacy.

The sample size used within this study is also relatively small and caution should be taken when interpreting the results. If preliminary evidence of effectiveness is found, an open trial followed by an RCT should be conducted to further examine the efficacy of the intervention, with RCT’s described as the ‘gold standard’ for effectiveness research [72].

Protocol version 1 (November 2021). Any changes to the protocol will be communicated to the journal and updated on ClinicalTrails.gov.
